### Outcomes of model implementation

The primary model implementation impact outcome is “Reach”, or the proportion of eligible CALD adults completing hypertension and/or diabetes screening. The primary implementation process outcomes are acceptability, appropriateness, and feasibility of the model of care, measured at the site and stakeholder level. Secondary outcomes include follow-up completion, treatment initiation, clinical control (BP and glycemia), intervention fidelity, program cost, and sustainability. Baseline measurements will be collected prior to implementation, with follow-up assessments occurring at 6 to 12 months post-implementation depending on the specific outcome (See Supplementary File 1). The sustainment component of EPIS framework and the RE-AIM evaluation framework will be utilized to guide assessment of these implementation outcomes related with implementation of the multi-packaged model of care. The RE-AIM framework is a widely used planning and evaluation tool in public health that helps assess the impact and scalability of health interventions across five key dimensions: Reach (the extent to which the target population participates), Effectiveness (the impact on important outcomes), Adoption (the extent to which settings and staff adopt the intervention), Implementation (how well the intervention is delivered as intended), and Maintenance (the extent to which a program is sustained over time) [35]. Originally developed to bridge the gap between research and real-world application, RE-AIM guides both the design and evaluation of programs to ensure they are not only effective in controlled trials but also practical and sustainable in everyday settings. However, some of the implementation outcomes in this study, specifically acceptability, appropriateness, feasibility, fidelity and cost are not native RE-AIM domains. These outcomes are intentionally drawn from Proctor et al.’s taxonomy to complement RE‑AIM’s implementation dimension with complementary measures being mapped pragmatically across the two frameworks [35, 36]. Reach will be calculated as the number screened divided by the number invited within each site and period based on community registries and screening logs. In addition, individuals who screen positive during each measurement period will form a nested cohort for follow up, and these clinical pathway outcomes will be summarised and analysed as site period proportions to remain consistent with the repeated cross-sectional design.

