
### Proposed tools for measuring implementation outcomes

There are various tools that have been utilized to assess various implementation outcomes across the literature. We will be using different adapted tools including the Acceptability of Intervention Measure (AIM), Intervention Appropriateness Measure (IAM), and Feasibility of Intervention Measure (FIM), psychometrically validated tools developed to assess key early-stage implementation outcomes. Each of these instruments consist of four items, rated on a five-point Likert scale from “completely disagree” to “completely agree.” The AIM captures the degree to which stakeholders find an intervention agreeable or satisfactory, making it a useful measure of perceived acceptability. The IAM evaluates whether an intervention is perceived as a good fit or relevant for a given context or problem, thereby assessing its appropriateness. The FIM measures the perceived practicality and ease with which an intervention can be successfully implemented in a specific setting. These tools are designed for ease of use, brevity, and reliability, making them highly suitable for integration into implementation research and practice across diverse settings [37]. In addition, other tools will be utilized depending on the expected outcome measures including the Clinical Sustainability Assessment Tool (CSAT), Short Form, and the Program Sustainability Assessment Tool (PSAT), Short Form, for model implementation sustainability assessment (Table 2).

**Table 2 Tab2:** Implementation outcomes and proposed assessment tools for the model of care

	Constructs	Assessment tools/Measures	Source of data	Method
RE‑AIM Implementation Evaluation Framework with Proctor et al. style implementation outcomes	Reach	Participation rate: % of individuals invited who actually undergo screening for the target NCDs.	Registry lists and clinical records	-
	Effectiveness	Follow-up rate: % of screen-positive individuals who receive timely confirmatory diagnosis and/or treatment.	Clinical records	-
		Proportion of people with controlled hypertension and diabetes among those diagnosed.	Clinical records	-
				-
	Adoption	Proportion of implementing agents/staffs that deliver model of care components.	Clinical records	-
	Implementation			
	✓ Acceptability	Acceptability of Intervention Measure (AIM) 4-items [37].	Implementing site staff members	Survey

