With regards to the sample size for this quasi-experimental study using the Difference-in-Differences approach, we have considered a hypertension prevalence of 34%, and an assumed baseline screening rate of 50% based on previous literature which shows that only one in two people detected to have hypertension are aware of their condition among the Australian population [4, 5]. Our target is to increase hypertension screening rates among CALD communities from 50% at baseline to at least 70% post-intervention, representing a 20% increase. To detect this difference with 80% power and a 5% significance level, we first calculated the sample size for comparing two independent proportions, assuming individual randomization. This yielded an unadjusted sample size of approximately 182 participants (91 per group).

Nevertheless, given the study’s clustered design involving 12 sites (six intervention and six control clusters), it is necessary to adjust for the expected intra-cluster correlation (ICC), which accounts for the similarity of responses within clusters. This adjustment is done by applying a design effect, calculated as: Design Effect (DE) = 1 + (m − 1) × ICC, where “m” is the average number of participants per cluster. In this study, we expect to recruit 100 participants per cluster and assume an ICC of 0.02 [41]. Applying these values, the design effect becomes: DE = 1 + (100 − 1) × 0.02 = 1 + 99 × 0.02 = 2.98. Applying this yielded an adjusted total sample size of approximately 543 participants, or about 272 per arm. Therefore, with the 100 expected participants from each cluster, the final planned sample size of 1,200 exceeds the minimum requirement and ensures sufficient power to detect the expected effect while remaining practical. Furthermore, the qualitative component will also include in-depth interviews, and stakeholder workshops with CALD communities, healthcare providers, and policymakers to explore perceptions, implementation processes, barriers, and enablers.

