### Data analysis plan for the main model

The Difference in Differences approach will be used to compare changes in hypertension and diabetes screening uptake between intervention and control sites over time with a repeated cross-sectional design. A Generalized Estimating Equations model will be utilized as the primary analysis method with site clustered robust standard errors and an appropriate small sample correction to account for the limited number of clusters. In addition, a generalized linear mixed model with a site level random intercept will be used as a sensitivity analysis. Key participant characteristics including age, sex, region of birth, education, primary language, and baseline comorbidities will be included as covariates. Results will be presented as adjusted marginal effects with 95% confidence intervals. Baseline equivalence between intervention and control sites will be examined using standardized mean differences, and any identified imbalances will be controlled for in the modelling. The parallel trends assumption will be assessed indirectly through these baseline comparisons and sensitivity analyses as only one pre intervention time point is available. For secondary outcomes, follow up completion, treatment initiation, and clinical control will be derived from the nested cohort of screen positive individuals and will be summarised and analysed as site period proportions. Missing data will be handled using multiple imputation with additional sensitivity analyses to evaluate the robustness of findings. If individual level data are pooled across sites with fixed per site samples, design weights proportional to the site population of eligible invitees will be used to account for unequal selection probabilities (See Supplementary File 1).

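### Clinical control of BP and glycaemia is analysed only as a proportion controlled; a continuous analysis beside it would recover precision at little cost

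*Protocol article*

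**What the plan says.** The section on outcomes of model implementation makes BP and glycaemia a secondary outcome: "Secondary outcomes include follow-up completion, treatment initiation, clinical control (BP and glycemia), intervention fidelity, program cost, and sustainability". Table 2, under Effectiveness, gives the measure, taken from clinical records: "Proportion of people with controlled hypertension and diabetes among those diagnosed". The population is defined in the outcomes section: "individuals who screen positive during each measurement period will form a nested cohort for follow up". The data analysis plan then states that "clinical control will be derived from the nested cohort of screen positive individuals and will be summarised and analysed as site period proportions". The reason offered, in the outcomes section, is consistency with the repeated cross-sectional design.

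The article gives no size for the nested cohort, no expected control rate, no standard deviation and no power for this outcome. The only sample-size calculation, in the section on cluster size, concerns screening uptake.

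**The concern.** A BP reading or a glycaemic value carries more information than a controlled/not-controlled label, and the nested cohort is likely to be small at each site. The stated reason does not require the cut. The people in the nested cohort are followed as individuals, so each should have a screening value and a later one. The primary GEE in the same section already uses participant-level covariates under the same repeated cross-sectional design.

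Two steps need to be kept apart. The information loss comes from the cut. Collapsing to site-period level does not cause it, because site-period means of the continuous values would keep the information. What collapsing mainly gives up is adjustment for each person's own screening value.

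At stake is the precision of half of what Table 2 lists under Effectiveness. An imprecise null on control could be read as no clinical benefit.

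**Working it through.** **1. The plan's own figure.** The plan sets out "To detect this difference with 80% power and a 5% significance level" a rise "from 50% at baseline to at least 70% post-intervention". Two-sided, unpooled: (1.960 + 0.842)² × (0.25 + 0.21) / 0.20² = 90.26, so 91 per group and 182 in total. Design effect: 1 + 99 × 0.02 = 2.98. Then 182 × 2.98 = 542.4, so 543. This reproduces the plan. It says nothing about clinical control.

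**2. Size of the nested cohort.** The plan says "we have considered a hypertension prevalence of 34%, and an assumed baseline screening rate of 50" per cent, with 100 participants per cluster and "12 sites (six intervention and six control clusters"). Hypertensive people per site-period:
- 100 screened: 100 × 0.34 = 34.
- 100 invited, 50% or 70% screened: 17 or 23.8.
- 1,200 covering both periods, so 50 invited per site-period: 8.5 or 11.9.

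The plausible range is therefore 8.5 to 34. The 70% is the post-intervention target, so it does not describe baseline or control sites. I use 20 below.

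For diabetes, assuming the 6.6% national prevalence from the Background: 100 × 0.066 × 0.5 = 3.3 and × 0.7 = 4.6, about 3-5 per site-period.

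**3. Information lost by the cut alone.** For a normal outcome with proportion p controlled and normal density φ at the cut point c, relative efficiency is φ(c)² / [p(1 − p)]. The loss is 36% at p = 50%, 38% at 40/60%, 42% at 30/70%, 51% at 20/80% and 66% at 10/90%. Once site-period clustering is counted, with 30-50% controlled and effects of 0.3 to 0.5 SD, the loss in the difference-in-differences contrast is 21-36% at ICC 0.02 and 11-32% at ICC 0.05.

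**4. Power.** From the plan: six sites per arm and ICC 0.02 (set for screening, borrowed here). Assumed: SD 18 mmHg; a cut at 140, for illustration only; mean 140 or 145 without the model; 20 per site-period, so N = 6 × 20 = 120 per cell; two-sided 5% test; noncentral t on 10 df; no dropout.
- Design effect: 1 + 19 × 0.02 = 1.38.
- Continuous: SE = √(4 × 18² / 120 × 1.38) = 3.86 mmHg. For 8 mmHg, 8 / 3.86 = 2.07.
- Adjusted for a screening value with correlation 0.5: SE = 3.86 × √0.75 = 3.34, and 8 / 3.34 = 2.39.
- Proportion, mean 140: p0 = 0.500, p1 = 0.672. SE = √[(3 × 0.250 + 0.220) / 120 × 1.38] = 0.106, and 0.172 / 0.106 = 1.63. With mean 145: p0 = 0.391, p1 = 0.566.
- A dichotomised variable has a lower ICC than the underlying one. Scaling it by the efficiency (0.02 × 0.637, design effect 1.24) gives the upper end of the proportion's range below.

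| Effect | Proportion controlled | Continuous | Continuous, adjusted |
|---|---|---|---|
| 5 mmHg | 15-17% | 22% | 27% |
| 8 mmHg | 31-36% | 47% | 58% |

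The same formulae for 8 mmHg at the ends of the cohort range, with equal numbers in both periods:
- 8.5 per site-period (SE 5.41): 18-20%, 27% and 34%.
- 34 per site-period (SE 3.25): 42-50%, 60% and 73%.

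The ordering is the same throughout.

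**The case against.** The strongest case for the plan is that nothing in it is misstated. Clinical control is one of several secondary outcomes, and the power claim is confined to screening. The proportion controlled is a recognised programme-level indicator and answers the question Table 2 asks; a mean difference in mmHg answers another. Site-level summaries are legitimate with 12 clusters. This stands, and it is why the proportion should stay.

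A reader might infer more than the documents support, in four ways.
- That a fixed third of the information is lost. That figure needs a normal outcome and a control rate near 50%, and the article gives neither. People selected for a positive screen may not follow a normal distribution.
- That site-period analysis is itself the fault. It is not; the cut is.
- That a real effect would be missed because of this choice. On the same assumptions, even adjusted continuous BP has 58% power at 8 mmHg, and the few sites and screen-positives limit both forms. At 5 mmHg the unadjusted gain is only about 5 to 7 points.
- That thresholds are unjustified. The article refers outcome and analysis detail to Supplementary File 1, which is not shown.

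Two further cautions stand. The correlation of 0.5 is assumed and may be lower in people selected on a high reading. For glycaemia no power can be computed: the article names no measure, and the records may hold more than one.

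**Conclusion.** The point holds as an efficiency weakness in a secondary outcome. It is not a contradiction or an arithmetic error, and it does not touch the primary analysis. The main text fixes clinical control as a proportion and gives a reason that does not require the cut. The cut costs roughly 21-36% of the information in the difference-in-differences contrast at ICC 0.02 with 30-50% controlled, and 36% or more without clustering. On the assumed values, continuous BP gains about 11 to 16 points of power at 8 mmHg before adjustment (47% less 31-36%) and 22 to 27 after it (58% less 31-36%). The SD, cut, means, effects and correlation are assumptions, not document figures, and applying ICC 0.02 to BP is another. The size of the gain is uncertain; its direction is not, in any of the settings worked through. Power remains limited in either form.

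**What to change.** In the data analysis plan, keep the proportion controlled by site and period as the reported programme indicator. Add a prespecified difference-in-differences analysis of continuous follow-up BP, adjusted for the person's screening value. Either the participant-level GEE already planned for the primary outcome, with site clustering and the small-sample correction, or an analysis of site-period means would serve.

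Do the same for glycaemia where one common measure is recorded across sites, and say in advance that the numbers may be too small for more than description.

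The cost is one or two extra models, using BP values the clinical records should already hold. The drawback is that a mean difference is less direct for programme managers than a percentage controlled, which is why the percentage stays in the report.

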### Patient and public involvement

No patients or members of the public were involved in developing this protocol. Nevertheless, PPIs, CALD community members, religious and community leaders, representatives from the Brisbane City health department, and other relevant bodies will be engaged during Phase I and subsequent stages to ensure that the research and the proposed model of care are culturally and contextually appropriate, based on their contextual requirements.

### Work plan

This implementation research is designed to be carried out over a five‑year period to ensure the systematic planning, phased execution, and rigorous evaluation of all project components. The quantitative follow up window for outcome assessment is 6 to 12 months after site activation, with any longer activity focused on qualitative work, sustainment assessments, and dissemination. A comprehensive description of the overarching operational plan, including methodological procedures, timelines, and implementation strategies, is provided in Supplementary File 1. In addition, the overall plan has been schematically depicted as follows to further aid conceptualization of the study design (Fig. 3).

**Fig. 3 Fig3:**

Duration of the different phases in the implementation research process to enhance access to and utilization of health services for the target NCDs among CALD communities in Brisbane city, Australia

### Limitations

A potential limitation of this protocol is its focus on faith-based settings, which may limit the generalisability of the co-developed model to secular or non-religious contexts and to CALD communities who do not engage with religious institutions. While some of these religious organisations (e.g., churches, mosques, and temples) may focus on specific CALD communities, many provide services to the wider population irrespective of cultural or religious background. Therefore, the selection of specific organisations in the final stages will depend on relevance and feasibility considerations, which may limit the representativeness of the settings included.

## Data Availability

No datasets were generated or analysed during the current study.

## Abbreviations

AIM: Acceptability of Intervention Measure
EBP: Evidence Based Practice
CALD: Culturally and Linguistically Diverse
CFIR: Consolidated Framework for Implementation Research
CSAT: Clinical Sustainability Assessment Tool
EPIS: Exploration, Preparation, Implementation, and Sustainment
FIM: Feasibility of Intervention Measure
ICC: Intra-Cluster Correlation
IAM: Intervention Appropriateness Measure
NCDs: Non-Communicable Diseases
PRISMA-ScR: Preferred Reporting Items for Systematic Reviews and Meta-Analyses Extension for Scoping Reviews
PSAT: Program Sustainability Assessment Tool
RE-AIM: Reach, Effectiveness, Adoption, Implementation, and Maintenance
